## Abstract

**Background::**

Surgery is generally accepted as the main therapeutic option for symptomatic lumbar spondylolisthesis. However, new nonsurgical therapeutic options need to be explored for this population.

**Objectives::**

The objective of this study is to assess the effectiveness and safety of a 5-week Mokhuri treatment program compared with conventional nonsurgical treatments for symptomatic lumbar spondylolisthesis.

**Methods::**

This is a study protocol for a multinational, multicenter clinical randomized controlled trial comparing the effectiveness and safety of 5 weeks of nonsurgical integrative treatments (a Mokhuri treatment program consisting of Chuna, acupuncture, and patient education) with nonsurgical conventional treatments (drugs for pain relief, epidural steroid injections, and physical therapy). Clinical outcomes including visual analogue scale (VAS) scores ranging from 0 to 100 for low back pain and leg pain, EQ-5D scores, Oswestry disability index (ODI) scores, Roland–Morris Disability Questionnaire (RMDQ) scores, Zurich Claudication Questionnaire (ZCQ) scores, walking duration and distance without leg pain, and a 5-minute treadmill test, and the ratio between the actual duration of participation and the originally scheduled duration in each group, the presence of any additional spondylolisthesis treatments, the types of concomitant treatments during the follow-up period, and adverse events (AEs) will be assessed at 7 weeks, 18 weeks, 30 weeks, 54 weeks, and 102 weeks after the end of the treatments.

**Conclusion and discussion::**

The results of this study will provide clinical evidence on nonsurgical integrative interventions for patients with symptomatic lumbar spondylolisthesis.

**Clinical trial registry::**

clinicaltrials.gov (NCT03107468)

## Introduction

1

Degenerative lumbar spondylolisthesis is a chronic spinal condition that causes instability of the segmental spinal bones due to degenerative changes in the spinal joints. According to a cross-sectional study released in 2009, the prevalence rate of degenerative lumbar spondylolisthesis was estimated to be as high as 13.6% in an adult community-based population, which suggests that a considerable proportion of general population have this condition.^[1]^ Most people with lumbar spondylolisthesis do not have any symptoms, and only approximately 10% of this population have clinical symptoms that require treatment. However, once symptoms occur, more than 50% of the patients complain of considerable pain and dysfunction and in severe cases, cauda equina syndrome.^[2]^

Nonsurgical conservative treatments are recommended for patients with symptomatic spondylolisthesis as a first-line therapy, but surgical treatments are considered in cases of failure of conservative treatments.^[3]^ Surgical interventions are performed to achieve decompression of nervous tissue, to relieve joint instability, and to lead to a comparatively good prognosis.^[4]^ However, considerable complication rates related to surgical interventions and considerable reoperation rates after spinal surgery have been reported.^[5,6]^ In addition, surgical treatment should be avoided if the patient has severe chronic conditions, multilevel stenosis, osteoporosis, or poor compliance.^[3]^ Considering this, nonsurgical interventions are recognized as an important option for the management of lumbar spinal spondylolisthesis.

According to the results of our previous observational study involving Mokhuri nonsurgical integrative treatments performed on patients diagnosed with Meyerding grade 2 lumbar spinal spondylolisthesis, considerable clinical improvement was observed after nonsurgical integrative treatments; the average walking distance without pain increased from 55 to 165 m, while the intensity of pain experienced when walking was reduced by 80% compared with the baseline assessment.^[7]^ In another previous retrospective audit study, on a numeric rating scale from 0 to 10, 44 spondylolisthesis patients reported a reduction in numeric rating scale scores from 7.1 to 3.1, and walking distance without pain increased from 193 to 568 m after treatment.^[8]^ These observational studies provide clues for the potential benefit of nonsurgical integrative treatments and suggest that these treatments might be effective for pain relief and functional restoration in patients with symptomatic lumbar spinal spondylolisthesis. However, observation studies cannot provide clinical evidence, so these new therapeutic options should be evaluated through rigorous, high-powered clinical trials.

The objective of this study is to assess the effectiveness and the safety of a 5-week Mokhuri treatment program compared with conventional nonsurgical treatments for symptomatic lumbar spondylolisthesis.

## Methods

2

### Study design

2.1

This is a study protocol for a multinational, multicenter clinical randomized controlled trial that is designed to evaluate the effectiveness and safety of nonsurgical integrative treatment in patients with symptomatic lumbar spinal spondylolisthesis who continue to have symptoms after a sufficient duration of conservative treatment. Patients with symptomatic lumbar spinal spondylolisthesis will be randomly allocated to one of the interventions: a 5-week Mokhuri treatment program (Chuna, acupuncture, and patient education) or nonsurgical conventional standard treatment (drugs for pain relief, epidural steroid injections, and physical therapy). The trial participants who agree to participate in the clinical trial after written informed consent will undergo the required examinations and tests according to the plan for the clinical trial. After 5 weeks of treatment, the clinical outcomes of both groups will be evaluated during follow-up, which will take place at 7, 18, 30, 54, and 102 weeks after the end of the treatments.

### Study setting

2.2

The trial will be conducted at the Mayo Clinic in the United States and the Mokhuri Oriental Medicine Hospital in Korea. Participants will be recruited at the division of Pain Medicine at the Mayo Clinic in Minnesota, US and at the Mokhuri Oriental Medicine Hospital in Seoul, South Korea. Participants will be recruited through flyer advertisement within the hospital, e-mail alert campaigns, and public advertisement. Any included patients will undergo 5 weeks of treatments in the outpatient unit and up to 96 weeks of follow-up evaluations.

### Inclusion and exclusion criteria

2.3

Individuals who meet all the following criteria will be included as appropriate participants in the clinical trial:(1)Those aged from 19 to 78 years;(2)Those with a diagnosis of degenerative lumbar spinal spondylolisthesis or who have low back pain, lower limb radiating pain, or leg discomfort when standing or walking with a severity of at least 5 on a visual analogue scale (VAS) of 0 to 100 for each symptom;(3)Those suffering from neurologic claudication or radicular pain for at least 1 year;(4)Those with neurogenic claudication within 5 minutes of walking on a treadmill at a speed of 1.5 miles per hour;(5)Those who have not received an epidural injection within the past month;(6)Those who have not undergone lumbar surgery;(7)Those who have confirmed spondylolisthesis on lumbar spine AP, lateral, nd both oblique views;(8)Those who weigh 250 lbs (113.398 kg) or less;(9)Those whose height is 2.1 m (6.890 ft) or shorter; and(10)Those who agreeing to participate in this clinical trial after receiving a thorough explanation of the purposes and characteristics of the trial and who are willing to sign the written informed consent form.

Participants who have any of following conditions will be excluded:(1)Those with a past or current history of diseases that cause ambulatory functional disability;(2)Those with knee joint and hip joint disorders that severely limit walking (i.e., moderate or severe osteoarthritis of the knee or hip joints);(3)Those who have been previously diagnosed with peripheral blood vessel diseases or vascular diseases, those who show an ankle-brachial index below 0.9 or those who have been diagnosed with peripheral arterial disease by Doppler ultrasonography of lower limbs, if necessary;(4)Those with severe diseases (cardiac disorders or renal insufficiency) to such a degree that an ambulatory evaluation cannot be performed;(5)Those with other specific spinal diseases (ankylosing spondylitis, spinal osteomyelitis, metabolic diseases, severe osteoporosis, etc.);(6)Those with severe neurological defects including foot drop or cauda equina syndrome;(7)Those with spinal instability confirmed by lumbar spine X-ray flexion and extension views, where spinal instability will be defined as observing one or more of the following: 4.5 mm sagittal plane translation, 20 degrees of sagittal plane rotation at L4-5, or 25 degrees of sagittal plane rotation at L5-S1;(8)Those with malignancies;(9)Those with past or current psychiatric conditions, such as major depressive disorder, anxiety disorders, panic disorders, or episodes of mania, delusion, and schizophrenia;(10)Those using narcotic analgesics including external dosage forms or patches;(11)Those women who are pregnant, lactating, or planning to become pregnant;(12)those who appear to be likely to encounter difficulties in adhering to this protocol; and(13)Those subjects whom the clinical investigators judge to be inappropriate.

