### Outcomes

2.10

The validated English version for the Mayo Clinic and the Korean version for the Mokhuri hospital will be used for all the outcome assessments. Outcome assessors will be blinded to the allocation results.

The primary outcome will be VAS scores from 0 to 100 for low back pain. The degree of pain will be evaluated on a 100 mm straight line, where the left edge of the straight line will indicate “0: no symptoms,” and the right edge will indicate “100: the most severe pain.” The participant will indicate the average level of lumbar pain experienced for the past week.

The secondary outcomes will include VAS scores from 0 to 100 for leg pain, EQ-5D scores, Oswestry disability index (ODI) scores, Roland–Morris Disability Questionnaire (RMDQ) scores, Zurich Claudication Questionnaire (ZCQ) scores, walking duration and distance without leg pain, a 5-minute treadmill test, the ratio between the actual duration of participation and the originally scheduled duration in each group, the presence of any additional spondylolisthesis treatments, the types of concomitant treatments during the follow-up period, and adverse events (AEs).

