### Sample size

2.12

To calculate the sample size, a retrospective study performed on 44 patients with lumbar spinal spondylolisthesis^[8]^ and the previous clinical trial data that assessed physical therapy for hospitalized patients in a similar study setting^[18]^ were used. To determine a meaningful difference between groups, a minimal clinically important difference of 2.5 points on the numeric rating scale of 0 to 10 was used.^[19]^ The standard deviation (SD) was 4.65 from the abovementioned previous studies. For the sample size calculation, the significance level (α) was 0.05, and the power (1–β) was 0.80. The following formula was used for the calculation. Assuming a drop-out rate of 10%, 61 participants will be needed in each study group, yielding a total of 122 participants needed for this study. 
[figure not shown]

In terms of the total 122 participants in the study, 108 participants will be recruited at the Mokhuri Oriental Medicine Hospital and 14 participants at the Mayo Clinic.

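### Inclusion criterion 2 admits participants with little or no low back pain, the primary outcome, which erodes the planned 25-mm difference and the stated 80% power

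*Protocol article*

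**What the plan says.** All references are to the protocol article.

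- **Section 2.3, criterion 2**, opens with "Those with a diagnosis of degenerative lumbar spinal spondylolisthesis or who have low back pain, lower limb radiating pain, or leg discomfort when standing or" walking, and closes with "with a severity of at least 5 on a visual analogue scale (VAS) of 0 to 100 for each symptom". The diagnosis and the symptoms are alternatives, and the severity threshold follows the symptoms.
- **Section 2.3, criteria 3 and 4**, are the only other symptom criteria: "Those suffering from neurologic claudication or radicular pain for at least 1 year" and "Those with neurogenic claudication within 5 minutes of walking on a treadmill at a speed of 1.5 miles per hour". Neither mentions low back pain.
- **Section 2.3, criterion 7**, requires spondylolisthesis confirmed on radiographs.
- **Section 2.10** states: "The primary outcome will be VAS scores from 0 to 100 for low back pain". On measurement it says "The degree of pain will be evaluated on a 100 mm straight line", with zero meaning no symptoms.
- **Section 2.12** states that "a minimal clinically important difference of 2.5 points on the numeric rating scale of 0 to 10 was used", with SD 4.65, alpha 0.05, power 0.80, 10% drop-out and 61 per group.
- **Section 2.13** analyses change from baseline by ANCOVA, with baseline score and institution as covariates.
- **Introduction**: the 44-patient audit that also feeds the sample size reports a mean pain score of 7.1 of 10 before treatment and 3.1 after.
- **Section 2.10** also has an early-termination rule with a cut-off below 1 on the 0–100 VAS.

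**The concern.** The entry criteria and the primary outcome do not match, for two reasons.

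First, 5 mm on a 100-mm line is close to no pain. Second, the threshold need not apply to low back pain at all: the diagnosis alone satisfies criterion 2, and so does a leg symptom. Criteria 3 and 4 keep the population symptomatic, but through leg symptoms.

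A score cannot fall below zero, so improvement is capped at the baseline value. Participants who enter near the floor contribute little or nothing to a between-group difference in improvement. The sample size assumes a 25-mm mean difference over everyone randomised. If a material share has no room to improve, the trial could miss a treatment effect that is present in patients who do have back pain. Including baseline as a covariate does not create room that is not there, and under the planned intention-to-treat analysis such participants cannot be removed afterwards.

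**Working it through.** **1. The plan's own figure.** Inputs from Section 2.12: difference 2.5, SD 4.65, alpha 0.05 (taken as two-sided), power 0.80.

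n per arm = 2 × [4.65 × (1.960 + 0.842) / 2.5]² = 54.3. Dividing by 0.9 for drop-out gives 60.3, rounded up to 61. The stated 61 per group reproduces, so the arithmetic is not at fault. About 55 per arm are evaluable (61 × 0.9 = 54.9).

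**2. Conversion to the outcome's scale.** 2.5 of 10 is 25 mm, and SD 4.65 is 46.5 mm if it is on the same 0–10 scale.

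**3. Room to improve.** At a baseline of 5 mm the largest possible improvement is 5 mm, one fifth of 25 mm. At 0 mm it is none. Among people entering at 5 mm, a 25-mm between-group difference could arise only if the comparator mean worsened by at least 20 mm.

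**4. Strictest reading of criterion 2.** If the words about each symptom mean that every listed symptom must reach the threshold, low back pain is guaranteed only to be 5 mm or more. The mismatch remains.

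**5. Effect on power.** Let f be the share with little or no low back pain at entry. The document gives no value, so 10%, 20% and 30% are assumptions. The others are taken to differ by 25 mm. Power is for a two-sided two-sample t test with 55 per arm and non-centrality d / (SD × √(2/55)), where √(2/55) = 0.1907. With no dilution this is 25 / (46.5 × 0.1907) = 2.819, power 80%.

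- **A.** No effect in the share, SD unchanged: d = 25(1 − f).
- **B.** A 5-mm effect in the share, SD unchanged: d = 25(1 − f) + 5f.
- **C.** No change at all in the share, so it adds no variance within itself. The others change by 4.0 points (7.1 − 3.1, from the audit) against 1.5 (2.5 less, assumed). On the 0–10 scale the variance per arm is (1 − f) × 4.65² + f(1 − f) × m², with m = 4.0 or 1.5, averaged over the arms. The pooled SD is 4.50, 4.33 and 4.13 for the three shares, and d = 2.5(1 − f).

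| f (assumed) | A: d, power | B: d, power | C: d, power |
|---|---|---|---|
| 10% | 22.5 mm, 71% | 23 mm, 73% | 22.5 mm, 74% |
| 20% | 20 mm, 61% | 21 mm, 65% | 20 mm, 67% |
| 30% | 17.5 mm, 50% | 19 mm, 57% | 17.5 mm, 60% |

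**6. Sample-size equivalent.** Under B, with the normal-approximation formula of step 1 rounded up before drop-out, 80% power needs 65, 77 and 95 evaluable per arm, or 73, 86 and 106 after dividing by 0.9. On that rounding the plan's own number is 62.

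**The case against.** Several stronger readings are tempting and should be resisted.

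- **That 25 mm is out of reach for low-baseline participants, as if each had to achieve it.** Section 2.12 plans on a difference between group means, not on a target for the individual. The supportable statement is that these participants' improvement is capped and the mean difference is diluted.
- **That the symptom branch of criterion 2 never operates, because criterion 7 already requires spondylolisthesis.** Criterion 2 names a degenerative diagnosis, whereas criterion 7 asks only for a radiographically confirmed slip. A patient with a non-degenerative slip would still need the symptom branch.
- **That 5 of 10 was intended.** The sample size and the audit use 0–10, and the below-1 cut-off in Section 2.10 shows the same pattern on a 0–100 scale. This makes a scale slip plausible, but the document does not say so.
- **That the power loss is known.** The shares have no source. The only baseline figure, 7.1 of 10, does not suggest that low scores are common, although its pain site is not stated and its patients were selected differently. Scenario A alone overstates the loss if unaffected participants also add little variance, which is why a range is shown.

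It can also be said that ANCOVA is more efficient than the t test used here. With an assumed baseline correlation of 0.3 to 0.5, the 20% case of scenario A rises to 65–73%. The same gain would lift the undiluted figure above 80%, so the loss from dilution is not removed.

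Finally, criteria 3 and 4 define a claudication and radicular population, and the sponsor may want one. That is a legitimate choice, but it sits badly with low back pain as primary outcome and with an unqualified 80% power. What stands is the mismatch as written; no other criterion sets a minimum for low back pain.

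**Conclusion.** The point holds as a mismatch between an entry criterion and the primary outcome. As written, criterion 2 lets in participants with little or no low back pain, and their capped improvement pulls power below the stated 80%. The direction follows from the text. The size does not: roughly 71–74%, 61–67% and 50–60% for shares of 10%, 20% and 30% are illustrations. They rest on assumed shares, on 55 evaluable per arm, on the plan's SD applied to the 0–100 scale, and on a full 25-mm difference in everyone else. If few such patients present, the loss is small. This is not a detail that an article leaves to a fuller document, because the criterion is stated with its number, scale and connective. The sample-size arithmetic itself is sound.

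**What to change.** Amend criterion 2 in Section 2.3 in three respects:

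1. Make the symptom requirement apply in addition to the diagnosis (and, not or).
2. Include a minimum for low back pain, since that is the primary outcome.
3. State the intended threshold in 0–100 units, at a level consistent with the 25-mm planning difference. The sponsor must say what was intended; the document does not settle the value.

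Then reconcile the scale across Sections 2.3, 2.10 and 2.12. This includes the below-1 cut-off of the early-termination rule in Section 2.10, where the intended scale should be confirmed; no view is taken here on what that rule should be.

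The cost is an amendment of one criterion. Some patients with mainly leg symptoms would no longer qualify, so recruitment may be slower by an amount that the document does not allow one to estimate. If the sponsor prefers to keep these patients, the criterion should say so openly, and the 80% power should be qualified for the share expected to enter with little low back pain.

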### Interventions

2.4

All the participants in each group will undergo 5 weeks of treatments. In the Mokhuri treatment group, participants will undergo 10 sessions of acupuncture therapy, Chuna therapy, and consultation with physicians. In the control group, participants will be administered drugs every day, have 1 or 2 epidural steroid injections, and participate in 10 sessions of physical therapy for 5 weeks.

### Interventions in the Mokhuri treatment group

2.5

All the treatments in this group will be conducted by Korean Medical doctors in Korea and an acupuncture practitioner in the US, both with at least 5 years of clinical practice experience. All the treatments in this group will be offered twice a week for 5 weeks (a total of 10 sessions). For acupuncture treatment, points including both LI4, ST36, LV3, BL22, BL23, BL24, and BL25 will be selected for stimulation. Disposable sterile acupuncture needles (0.25 × 40 mm, Dong-bang Acupuncture, Seong-Nam, Korea) will be used. Chuna treatment, which is a kind of manual therapy consisting of relaxation and mobilization of the lumbar joint sand back muscles using an Ergo Style TM FX-5820 Table (Chattanooga Group, TN), will be conducted during every treatment visit. Participants will lie on the table in the prone position, and a practitioner will relax the back muscles of the patient, while the table causes the patient's spine to flex and extend automatically.^[9]^ Along with the acupuncture and Chuna treatment, patient consultation regarding advice for everyday life activities, walking, and particular movements and exercises will be offered to participants during every visit.

### Interventions in the control group

2.6

Participants in the control group will undergo 5 weeks of nonsurgical conventional standard treatments including drug therapy, epidural injections, and physical therapy. Through consultation with neurosurgeons or anesthesiologists or rehabilitation medicine specialists, drugs including muscle relaxants, NSAIDs, gabapentin, pregabalin or tricyclic antidepressants will be prescribed based on each patient's condition. Epidural steroid injections will be performed once or twice during the 5-week participation period. Physicians will assess the participants’ pain condition and decide whether they might need an epidural steroid injection at each visit. Physicians will re-evaluate the pain severity of the participant and perform epidural injections after a 2-week interval if necessary. Epidural injections will be performed at the affected spinal level. Physiotherapists will conduct physical therapies, including heating pad application for 10 to 20 minutes and transcutaneous electrical nerve stimulation for 5 to 10 minutes, twice a week during the 5 weeks of participation.

### Allowed cotreatments

2.7

According to the investigators’ decisions, medications that do not appear to influence the interpretation of the results of this clinical trial, such as medicines the participants have been taking for 4 weeks prior to participating, will be allowed. In addition, in both the Mokhuri treatment group and the conventional treatment group, participants will be allowed to continue using the same types of pain medications at the same doses and frequencies that they have been taking them before participating in this study.

### Research personnel training

2.8

One month of training for practitioners participating in the treatments will be planned at 5 days a week for 8 hours a day for 160 hours in total. The training program will include the theory of the treatments, the practice of Chuna, and patient education. A common standard operating procedure (SOP) for treatments will be provided, and practitioners will follow this SOP. At the end of every week, trainees will be evaluated for competence.

